## Methodology of the ICP–PMF Synergy

### Study design

Prospective observational study. The results of the observation will be analyzed according to the observed/expected approach (indirect standardized ratio) with the same outcomes observed in the population matching the study population for age and sex distribution, and location of residence. The analysis will consider three approaches in order to compare the outcomes: a) pooling all together the citizens who underwent whatever intervention vs the ones who did not undergo interventions; b) compare who underwent both social and health intervention vs the ones who receive only social or health intervention and vs the ones who did not undergo intervention; c) assess the impact of specific intervention against a control group set up specifically for this purpose.

The sources of the comparison will be mainly data already available from established data-flow at international, national and local level. To give an example data on hospitalizations are largely available at national and local level and could represent the standard of care against the outcomes of the planned intervention could be compared. Studies utilizing this kind of data, carried out by stakeholders involved in this proposal are ongoing [35–36].

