### Sample

Subjects for inclusion/assessment will be aged over 64 years and living at home; those living in an institution (nursing homes or similar) will be excluded. Each study site can decide to restrict the field of intervention with additional exclusion criteria. The total number of European citizens involved in the assessment will be around 2000 for each outcome of which at least 20% will be enrolled before the end of June 2016.

Participants will be enrolled among the ones who access the services managed by the stakeholders involved in the proposal. In Ireland, participation in the study will be offered to community-dwelling older adults who are under surveillance by their Public Health Nurse consistent with ongoing studies in this setting [10, 13, 14]; in Valencia participant will be the women who access the outpatients department of the University Hospital gynecologic service for health control. In Genoa participants to the DOREMI project will be enrolled enrolled involving citizens who access to the local University Hospital. In Barcelona participants will be enrolled among communitydwelling older adults who are attended by their primary health care team, both in the office and at home. In Twente and Campania, community dwelling older adults will be enrolled among participants to the PERSSILAA project, patients referring to Federico II outpatients practices and to the GPs of the Salute in Collina no profit organization. Campania study sample will also include participant to the Sunfrail pilot, and to the Beyond Silos project in Salerno. In Rome the over-74 citizens reached by the Viva gli Anziani program (all living in the community) will be included in the study. In Porto participants will be primary care patients of Health Centers that agreed to participate. People over 64 years will be prescreened by trained GPs and further assessed by the CARTS project team, supported by the General Directorate of Health. In Parma the over 64 citizens of Central District of Parma will be included as part of Sunfrail and SprinTT recruitment process. In Pecs community dwelling older adults will be enrolled from members and clients of local NGO’s Wherever possible the General Practitioner of the citizens involved in the study will be informed.

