### Sample size

– Alpha error = 5%– Power = 80%– Confidence Level = 95%– Confidence Interval = 1%– Population = 28,737,910^3^– Expected reduction of frailty incidence = 2.5%– Expected reduction of hospitalization rate = 5%– Expected reduction of Institutionalization rate = 5%– Expected reduction of death rate = 2.5%– Test 1 Proportion (observational study) superiority: sample size needed per single outcome = 2,000 subjects (including 10% of lost-to-follow up)^4^– Comparisons will be carried by applying the observed/expected approach on the basis of data stemming from the existing data flows available in the different study sites (national, regional or local data flow). The stratification of risk carried out by administering the baseline assessment will allow also transnational comparisons

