### Follow up

According to the different program/projects intervention schemes, follow up data will be gathered every six-twelve months. The follow up will consist of the information that will be obtained following the baseline assessment on incidence of frailty, hospitalization, institutionalization and death. The study will run for 36 months in total including three months set up time and three months at the end to finalize the assessment (Fig 2)

Table 3 reports the list of study site with the list of data sources to be considered in the study for the comparisons. In some cases different kind of control groups will be also used: historical or ongoing cohort of citizens, assessed for frailty with comparable tools, who did not underwent any intervention will be involved in the data analysis. Data will be analyzed every six months

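### The observed/expected ratio is standardised only for age, sex and residence although the cohort excludes institution residents and comes largely from service users, so selection alone can move it by as much as a relative 2.5–5% reduction

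*Protocol article*

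**What the plan says.** Only the Protocol article is at hand; no statistical analysis plan is shown.

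- **Comparison.** Study design makes an indirectly standardised O/E ratio the analysis, "with the same outcomes observed in the population matching the study population for age and sex distribution, and location of residence". No other variable is named. On sources: "The sources of the comparison will be mainly data already available from established data-flow at international, national and local level".
- **Cohort.** Sample states that "those living in an institution (nursing homes or similar) will be excluded", and that "Participants will be enrolled among the ones who access the services managed by the stakeholders involved in the proposal". The examples include public health nurse caseloads, hospital outpatients, a gynaecology clinic, primary-care patients and NGO clients. Rome is worded differently: "In Rome the over-74 citizens reached by the Viva gli Anziani program (all living in the community) will be included in the study".
- **Premise.** The operational definition of frailty ties the risk of hospitalisation, institutionalisation and death to frailty level and to socioeconomic resources.
- **Baseline risk.** Baseline assessment uses RISC and SFGE to stratify participants and to follow their risk by exposure to interventions. Sample size adds: "The stratification of risk carried out by administering the baseline assessment will allow also transnational comparisons". Follow up brings in, in some cases, an untreated "historical or ongoing cohort of citizens, assessed for frailty with comparable tools".
- **Targets.** Sample size gives reductions of 2.5% (frailty incidence, death) and 5% (hospitalisation, institutionalisation). For example, "Expected reduction of frailty incidence = 2.5"% does not say whether the figure is relative or in percentage points.

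**The concern.** Indirect standardisation answers the study's question only if participants, left without the programme, would have had the reference rates for their age, sex and area. Two features of the cohort work against this.

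1. The reference is described as routine population data, and nothing restricts it to people living at home. If institution residents are in it, their deaths and admissions raise the expected count for a cohort that contains none of them.
2. People in contact with health or social services may be sicker than others of their age and sex (nurse surveillance, outpatients) or healthier (health-control visits, club members).

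The article's own premise makes frailty the main driver of these outcomes, and frailty is what the standardisation omits. What is at stake is whether an O/E below 1 can be read as a programme effect. A larger sample does not remove this bias; it only narrows the interval around a shifted value.

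**Working it through.** **The plan's own figure.** The 2,000 per outcome, including 10% loss (1,800 evaluable), cannot be reproduced, because no base rate appears in the text at hand. One-sample proportion test, 80% power, 5% alpha:

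n = [(z_α√(p0(1−p0)) + z_β√(p1(1−p1))) / (p0−p1)]²

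- A 2.5-point drop gives 1,800 at p0 of about 18% (two-sided) or 25% (one-sided).
- A 5-point drop never needs more than 783 evaluable for p0 up to 50%.
- At rates of 5–20%, a relative 2.5% drop needs about 43,700–263,000 after inflation for loss, and a relative 5% drop about 10,800–65,300.
- A ±1% precision formula at p = 5% gives 1.96² × 0.05 × 0.95 / 0.01² = 1,825, or 2,028 after dividing by 0.9.

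The targets may therefore be percentage points, and both readings are carried below.

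**How much of the study is exposed (Table 3).** Official sources are listed for Barcelona (1,000), Genova (30), Naples (175), Parma (1,000), Pecs (200) and Rome (4,500): 6,905 of 15,205, or 45%. Parma and Pecs (1,200) list nothing else.

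Every input below is an assumption; the article gives none. Each ratio must hold within age-sex strata, since age and sex are already standardised.

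**Institution exclusion, death.** Let q be the institutional share of the reference and R the residents' risk ratio against community dwellers. With no effect, O/E = 1/(1−q+qR).

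- q = 1%, R = 1.5: 1/1.005 = 0.995
- q = 3%, R = 3: 1/1.06 = 0.943
- q = 5%, R = 5: 1/1.20 = 0.833

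Risk ratio needed to produce a spurious reduction, R = 1 + (1/target − 1)/q:

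| q | O/E 0.975 | O/E 0.95 |
|---|---|---|
| 1% | 3.6 | 6.3 |
| 2% | 2.3 | 3.6 |
| 3% | 1.9 | 2.8 |
| 5% | 1.5 | 2.1 |

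**Institution exclusion, new institutionalisation.** If existing residents stay in the denominator but contribute no new admissions, O/E = 1/(1−q): 1/0.99 = 1.010 to 1/0.95 = 1.053. This bias runs the other way.

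**Service-user selection.** Let s be the users' share of the population and k their risk ratio against non-users. O/E = k/(sk+1−s). At s = 30%:

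- k = 0.8: 0.8/0.94 = 0.851
- k = 1.5: 1.5/1.15 = 1.304
- k = 2: 2/1.3 = 1.538

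**Percentage-point reading.** Bias = rate × |1 − O/E|.

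- O/E 0.943: 0.29 points at a 5% rate, 1.14 at 20%
- O/E 0.833: 0.83 points at 5%, 3.3 at 20%
- O/E 1.30: 1.5 points at 5%, 6.0 at 20%

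**False benefit.** True effect nil, O/E = 0.943, expected rate p treated as fixed, nominal 2.5% in the direction of benefit: Φ{[(1−b)p − 1.96√(p(1−p)/n)] / √(bp(1−bp)/n)} with b = 0.943.

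| Evaluable n | p = 5% | p = 20% |
|---|---|---|
| 1,800 | 7% | 22% |
| 6,214 (6,905 × 0.9) | 17% | 62% |
| about 13,700 (15,205 × 0.9) | 33% | 92% |

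**The case against.** - **The baseline score has uses.** A reader might infer from the standardisation set that the score goes unused, or serves only comparisons between countries. The article does not support that: it stratifies participants by risk, follows risk by exposure, mentions transnational comparison as a further use, and adds frailty-assessed cohorts at some sites. Routine data would not usually carry the score in any case. What stands is that it is not named in the O/E comparison.
- **The size is assumed.** A reader might infer that the bias exceeds the effects sought. The article gives no institutional share, risk ratio or frailty mix, and the mildest inputs leave O/E at 0.995. The stated sample size also fits percentage points better than a relative reading. On points, the institution exclusion alone reaches 2.5 only at the harsher inputs and higher rates. This objection stands, so the claim is only that bias can be of that order.
- **Other comparators exist.** Study design also plans comparisons of treated with untreated people and with specific control groups. Cork, Galway, Oporto, Salerno, Twente and Valencia (8,300 planned) list no official statistics. This limits the reach of the point but leaves 6,905 participants with official sources.
- **Not everyone is a service user.** Rome enrols people reached by a programme and Parma describes pro-active screening. The direction of selection must be judged by site.
- **A later analysis plan could add variables.** It could, but the article states its standardisation set, and that set conflicts with its own premise.

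**Conclusion.** The point holds in this form: as written, the O/E standardisation omits institutional status, route of recruitment and baseline risk, so the ratio can depart from 1 with no programme effect. Under the assumed inputs the departure for death is about 0.83–0.995 from the institution exclusion, and 0.85–1.54 from service-user selection. This can equal or exceed a relative 2.5–5% reduction. On a percentage-point reading the institution exclusion is usually below target, while strong service-user selection can still exceed it (6.0 points at a 20% rate, against a 5-point hospitalisation target).

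No single net direction can be stated. Excluding residents lowers O/E for death, residents left in the denominator raise it for new institutionalisation, and recruitment can push either way. An O/E below 1 against general-population data therefore cannot by itself be attributed to the programmes.

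**What to change.** 1. Use community-dwelling reference rates, removing institution residents' events and person-time, wherever the data flow allows. Elsewhere, report a sensitivity range with the expected direction of bias by outcome and site.
2. Where an untreated cohort or control group was assessed with a comparable frailty tool and records the same outcome, make the main comparison one standardised on baseline risk stratum plus age, sex and site. Candidates in Table 3 are the control groups at Oporto (RISC only) and Salerno. The Lazio Region Frailty Study could serve Rome and Naples if its tool can be mapped to RISC or SFGE; the article does not say which tool it used. Twente can serve frailty incidence only, since it lists none of hospitalisation, institutionalisation or death.
3. Present O/E against the general population as supportive, not as evidence of programme effect on its own.
4. State whether the 2.5% and 5% targets are relative or percentage points, so that the bias can be judged against them.

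**Cost.** Analysis wording, plus requests for community-dwelling denominators that some data flows may be unable to meet. The baseline score is already collected. Fewer sites enter the main comparison, and its intervals are wider.

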### Baseline assessment

The baseline assessment aims to stratify the population, (from robust to frail individuals) according to the risk on negative outcomes. The basis of the stratification is the operative definition of frailty above-mentioned.

The tool to be used should:

Identify frail individuals and size the risk of hospitalization, institutionalization and death as well as the trend of this risk during the follow up according to the exposure to interventions to cope with frailtyCover the five domains of frailty: social and economic resources, functional status, physical and mental health;Be short and easy to administer in order to involve thousands of citizens;Be simple in order to involve non –health professional personnel, such as the care-giver to administer it.

The working group reached a consensus on two common instruments for baseline assessment:

The **Risk Instrument for Screening in the Community** can be used to quickly screen large numbers of patients to identify and stratify those at greatest risk of three adverse healthcare outcomes (institutionalisation, hospitalisation and death) [10, 13, 37–41]. These patients can then be triaged for further assessment, investigation and treatment with integrated care bundles or other management strategies that are location or service specific. The RISC tool collects demographics, records concerns, the severity and ability of the caregiver network to manage three main domains (mental state, ADL state and medical state issues). It then summarises the perceived risk using a subjective, global score of risk based upon a five-point Likert scale measured from 1 (minimal-rare risk) to 5 (extreme-certain). The RISC was developed as an exemplar under the EIP on AHA reference site COLLAGE, Ireland’s only reference site for active and healthy ageing. It has been translated into multiple languages (English, Dutch, Italian, Spanish and Portuguese). It has been validated in multiple sites in the EU as part of work conducted in Action Group A3 of the EIP on AHA including in Porto (34) and Barcelona. The RISC stratifies risk of adverse healthcare outcomes by measuring the magnitude of functional, physical or state mental concern.

Sometimes although the concern may be minimal, the lack of formal and/or informal caregivers may elevate or even multiple that risk.

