Parma	Over 64 (1000 ind.s)	Prospective observational	-Sunfrail -SFGE -RISC	-Pro-active frailty screening of 1000 over-65 citizens followed by comprehensive geriatric assessments -Referral to day services or day-hospital-based services in case of need -Strengthening the social network around the frails -Activation of nutritional, physical exercise and technological monitoring interventions with specific targets: -Prevention of falls -Prevention of negative consequences of social isolation -Prevention of Malnutrition	Incidence of frailty Progression of frailty Incidence of hospitalization Incidence of institutionalization Incidence of death	Official sources (report on the hospitalization and mortality in Emilia Romagna region released annually by ISTAT and Ministry of Health);
Pecs	Over 64 (200 ind.s)	Prospective observational	-SFGE -RISC	-Frailty screening -training of the target group) on ICT skills -training of informal caregiver network on the use novel assessment and training tools. -widespan public awareness raising campaign of the general public in all participating countries	Incidence of hospitalization Incidence of institutionalization Incidence of death	official statistical data of the National Health Insurance and Statistical Bureau
Oporto	Over 64 (300 Ind.s)	Prospective double arm observational	- RISC	-A training program for PC professionals on frailty and dementia screening and intervention -A awareness program for the general community on frailty and dementia issues. -A psycho-educational program for caregivers of old people frail or with dementia. -A cognitive stimulation program for people with cognitive frailty or MCI	Incidence of hospitalization Incidence of institutionalization Incidence of death	Control group
Rome	Over 74 (4500 ind.s)	Prospective observational	-SFGE -RISC	-Pro-active frailty screening/monitoring -Home visits -Assistance in bureaucratic tasks -Referral to formal community-based or hospital-based services in case of need -Strengthening the social network around the frails -Community-based social activities including health promotion with specific targets	Incidence of hospitalization Incidence of institutionalization Incidence of death	Official sources (report on the hospitalization and mortality in Campania region released annually by ISTAT and Ministry of Health); data stems from the ongoing Lazio Region Frailty Study carried out by the University of Tor Vergata,

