Salerno	Over 64 (100 ind.s)	two arms prospective observational	-SFGE -RISC	-Multidimensional assessment -Social and Health care integration -Electronic Clinical Record filled by the personnel and by the patient/caregiver -Home care monitoring and treatment by remote -Clinical management	Incidence of hospitalization Incidence of institutionalization Incidence of deaths	Control group
Twente	65–75 (300 ind.s)	two arms prospective observational	-GFI -SF-12 -SF-36 -MNA -SFGE -QMCI -NMA -Phys. test^6^	-frailty screening through multidimensional assessment -The PERSSILAA physical module Web-based exercising Monitoring	Incidence of frailty/functional decline Quality of LIfe	Control group
Valencia	Over 64 (1600 women)	Prospective observational	- Fried - CFS - SFGE - RISC	-Clinical assessments -Analytical Lab assessments -Bone metabolism assessment -Frailty assessment. -Cognitive frailty -Quality of life -Lifestyle intervention	Incidence of frailty Progression of frailty Incidence of hospitalization Incidence of institutionalization Incidence of death	pre and post-intervention assessment comparison with other cohorts within the working group (Twente)

**Table 4 t4-tm-15-53:** SPRINTS forecasted by the synergy proposal

N∘	Name	Starting date	Delivery date	Geographic coverage	Results
**S 1**	Set up a community - based public health approach to scale-up multidimensional screening tools in order to prevent, detect and manage frailty in community dwelling elderly. Target population and procedure to deliver the screening will be agreed. Ongoing interventions will be included into a common pathway defined by the assessment methodology.	15-Jan-2016	31-Mar-2016	Six Countries	Report on the action plan to implement a public health approach to frailty in community dwelling elderly and on the assessment methodology

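### Approaches (a) and (b) compare people by intervention received but standardise only for age, sex and residence, leaving confounding by need and, where intervention starts after baseline, immortal time

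*Protocol article*

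**What the plan says.** The Study design section of the protocol article describes a prospective observational study analysed by observed/expected ratios, with three approaches. Approach (a) is "pooling all together the citizens who underwent whatever intervention vs the ones who did not undergo interventions". Approach (b) is to "compare who underwent both social and health intervention vs the ones who receive only social or health intervention", and also against people with no intervention. Approach (c) uses a control group set up for a specific intervention. The reference for the observed/expected ratio is a "population matching the study population for age and sex distribution, and location of residence", and the comparison sources are mainly existing data flows.

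On the order of events, the Baseline assessment section says of people screened with RISC: "These patients can then be triaged for further assessment, investigation and treatment". In Table 3, the activities at Barcelona, Galway and Rome include "Referral to formal community-based or hospital-based services in case of need"; Parma has a similar entry for day services. On the start of observation, the Follow up section says: "The follow up will consist of the information that will be obtained following the baseline assessment".

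Two further statements bear on the point. Table 4 (sprint S1) says: "Ongoing interventions will be included into a common pathway defined by the assessment methodology". The Sample size section says: "The stratification of risk carried out by administering the baseline assessment will allow also transnational comparisons".

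**The concern.** In (a) and (b) the exposure is what a person received. If receipt depends on need, the treated group holds more people who were already likely to be hospitalised, institutionalised or to die. Age, sex and residence do not capture that: two people of the same age and sex in the same town can fall in very different RISC strata.

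A second problem arises if an intervention starts some time after baseline and people are classed as ever or never treated over the whole follow-up. A person who dies before the intervention could begin is counted as untreated, and the treated group is credited with time in which death was impossible by construction. In (b) this grows with each added type, because receiving two types requires surviving until the second.

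The first bias makes interventions look harmful and the second makes them look beneficial. The article wants to use the results to judge effectiveness and support scale-up, so it matters whether an observed ratio can be attributed to the interventions.

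**Working it through.** **The effect sought.** The Sample size section gives 5% alpha, 80% power, reductions of 2.5% (frailty incidence, death) and 5% (hospitalisation, institutionalisation), and 2,000 per outcome including 10% loss. No base rate is given, and it is not said whether the reductions are absolute or relative. With the one-proportion formula n = [z_α√(p0(1−p0)) + z_β√(p1(1−p1))]² / (p0−p1)²:

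- Absolute 2.5 points: p0 = 0.18, two-sided, n = 1,790, and 1,790/0.9 = 1,989. With p0 = 0.25, one-sided, n = 1,811, and 1,811/0.9 = 2,013. Mirror values of p0 (0.77-0.84) also fit.
- Absolute 5 points: at most about 870 after loss, so never 2,000.
- Relative 2.5% needs p0 of 0.85-0.88; relative 5% needs 0.58-0.64.

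The figure of 2,000 is therefore neither confirmed nor refuted, and both readings of the target must be kept.

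**Immortal time alone, no true effect.** Assumptions (none from the documents): constant hazard λ; half the cohort destined for intervention; start uniform over (0, W) years; follow-up F; the event prevents later treatment; the untreated come from the same cohort. Let p = 1 − e^(−λF) and A = (1 − e^(−λW))/(λW), the chance of being event-free at the start of intervention. Then

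- risk in ever-treated = 1 − (1−p)/A
- risk in never-treated = (p + 1 − A)/(2 − A)

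Example: p = 0.20, F = 1, W = 0.5 gives λ = 0.2231 and A = 0.9462. Treated: 1 − 0.8/0.9462 = 15.5%. Untreated: (0.20 + 0.0538)/1.0538 = 24.1%. Ratio 0.64.

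| Risk p over F | Starts spread over | Ratio | Spurious reduction (points) |
|---|---|---|---|
| 20%, 1 year | 3 / 6 months | 0.80 / 0.64 | 4.4 / 8.6 |
| 5%, 1 year | 3 / 6 months | 0.78 / 0.61 | 1.2 / 2.4 |
| 2.5%, 6 months | 1 / 3 months | 0.85 / 0.60 | 0.4 / 1.2 |
| 18%, 30 months | 1 / 3 / 6 months | 0.97 / 0.91 / 0.84 | 0.5 / 1.6 / 3.2 |

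The six-month row corresponds to the first impact assessment in Table 4 (S4). Thirty months is the 36-month study less three months of set-up and three of close-out.

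**Need alone, no true effect.** Assumptions: 30% frail; robust hazard 0.05 per year; one year; treatment starts at baseline.

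- Hazard ratio 2, 70% of frail and 40% of robust treated: frail share 0.21/0.49 = 42.9% of treated and 0.09/0.51 = 17.6% of untreated. One-year risks are 4.88% (robust) and 9.52% (frail), giving 6.87% against 5.70%: ratio 1.21, 1.2 points of apparent harm.
- Hazard ratio 3, 80% and 20% treated: frail share 63.2% and 9.7%, giving 10.59% against 5.75%: ratio 1.84, 4.8 points.

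**Both together** (same hazards, starts spread over 3 or 6 months): the ratio runs from 0.71 (hazard ratio 2, 70%/40%, 6 months) to 1.42 (hazard ratio 3, 80%/20%, 3 months). It is 1.03, near cancellation, at hazard ratio 3, 70%/40%, 3 months.

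**After counting pre-intervention time as unexposed.** Without confounding by need, the null rate ratio returns to 1.000. With need it stays at 1.16-1.21 (hazard ratio 2, 70%/40%) and up to about 1.7-1.9 (hazard ratio 3, 80%/20%), so baseline risk must be handled as well.

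**The case against.** Several points against a stronger reading are sound.

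- A reader might infer that immortal time affects (a) and (b) throughout. The article does not fix when exposure starts. It describes interventions already ongoing, and participants drawn from people already using the stakeholders' services or enrolled in their projects. An intervention already running at baseline creates no immortal time.
- The comparators are mainly external data flows, and early events among participants cannot move into an external population. The ratios for immortal time apply only to the treated-versus-untreated contrast inside a followed cohort, which (a) and (b) nonetheless state.
- A hospital stay in the first month does not prevent intervention in the fourth. The mechanism is secure for death and weaker for hospitalisation.
- A reader might infer that the biases far exceed the effect sought. That needs the 2.5-5% to be relative and rests on assumed rates and delays. Against an absolute 2.5-5 points, several scenarios above fall short, and the two biases can nearly cancel.
- Twente (65-75) and Rome (over 74) look like an obvious case of confounding by site, but Table 3 gives them no outcome in common. Pooling can also refer to intervention types; the article does not say that crude data are merged across sites.
- RISC and SFGE strata are collected, the Baseline assessment section wants the risk trend read by exposure, some control cohorts are assessed with comparable frailty tools, and (c) has dedicated controls.

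It is also fair that covariate adjustment and time-varying exposure are often left to an analysis plan, which is not shown. That does not dispose of the point. The article itself states the grouping rule and the standardisation variables, and the added use it names for the risk strata is transnational comparison. It does not tie them to (a) or (b).

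**Conclusion.** The concern holds in limited form. As stated, (a) and (b) group people by receipt, delivery at several sites follows need, and age, sex and residence cannot remove that. Confounding by need is the better-documented part. Immortal-time bias is conditional on intervention starting after baseline, an untreated group from the same cohort, and ever/never classification.

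Against a relative target (ratio 0.95-0.975), either bias alone is usually much larger; the mildest case shown, 0.97, is about the size of a 2.5% effect. Against an absolute target of 2.5-5 points, the bias ranges from well below it (0.4-0.5 points) to above it (8.6 points). Either bias can thus match or exceed the effect sought, and the net sign is unknown. All these sizes rest on assumed hazards, delays, frail share and treatment chances, because the article supplies none. They show what is possible and do not estimate the bias in this study.

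**What to change.** In the Study design section, state that (a) and (b) are stratified or adjusted by site and by baseline risk stratum, in addition to age and sex. Use whichever score the site collects: Table 3 lists RISC without SFGE at Oporto and SFGE without RISC at Twente.

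For interventions that start after baseline, count person-time and events before the first intervention as unexposed. In (b), likewise do not credit time before the second type starts to the both-types group. A landmark analysis is an acceptable alternative. State which interventions were already running at baseline, since they need only the risk adjustment.

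The cost is recording a start date for each intervention type and slightly more analysis work; no extra participants are needed. Residual confounding by need that RISC and SFGE do not measure will remain and should be acknowledged when (a) and (b) are reported.
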